### Structure to support sustainability and scale-up

In developing the support structure required for teachers to learn, implement, and sustain WD practices and for additional teachers to be trained, we focused on three areas: understanding the multilevel organizational structure of the school system; delivering professional development to teachers; and systematically monitoring teacher practices and support to teachers.

### Multilevel structure of the school system

To understand the level and nature of the mandate, authority, accountability, and resources necessary to sustain and scale-up WD practices, we needed to understand the multilevel organizational structure of the school system. Figure 2 presents the organizational structure at the time of the WD trial. The Board of School Commissioners (the school board) had the legal authority to oversee all operations of the school district. The chief executive officer (CEO) of the school district (the superintendent) oversaw all aspects of school district administration. The chief academic officer (CAO) served under the CEO and was responsible for all K through 12 instruction, academic as well as behavior and social emotional learning. Under the direction of the CAO, the city schools were divided into four elementary areas, a middle school area, and a high school area, each overseen by an area academic officer (AAO). AAOs were responsible for providing support to principals as well as to the schools more generally. Each area office had at least one coach who worked directly with schools to provide professional development. Within the school building, teachers were supported by the principal, school-based instructional coaches, and support staff such as social workers and psychologists.

**Figure 2 F2:**
[figure not shown]
**Multilevel Structure of a School System**.

We worked with the school system to create two teams to support the effectiveness trial and the goal of sustaining and scaling-up practices in the school system--the Core Team and the Schools Committee. The Core Team comprised individuals who held key positions of authority in the school system, along with senior members of the American Institutes for Research (AIR team). District members included the CAO, senior staff from the offices of curriculum and instruction and professional development, and the area superintendents whose schools were participating in the trial. The Core Team was responsible for the implementation and continued monitoring of the randomized field trial within the school district, and met monthly to review progress against benchmarks and to anticipate and resolve problems. The Core Team's role was also to address the challenges that often impede the uptake of interventions into general practice, including the time to deliver the intervention, the ease of implementation, the compatibility of the intervention with the mission and vision of the institution, and the cost of the intervention [1-3,18-29].

Principals of the 12 participating schools, along with Core Team members and senior AIR staff, participated on the Schools Committee. The committee met monthly to address issues pertinent to the field trial, such as maintaining fidelity, developing procedures for randomization of teachers/classrooms and students, engaging with parents and garnering consent, determining ways to introduce the field trial to the school community, maintaining the morale of standard classroom (comparison) teachers, and making decisions at the school level regarding oversight, monitoring, and allocation of resources.

### Professional development to teachers

As part of the WD trial, we addressed the primary concern of school system leaders with regard to professional development for teachers, namely, that the role of the WD facilitator be specified with precision so that practices would be observable and replicable. Because we were interested in building capacity within the school system, we decided that AIR staff would not train teachers directly but would train school district employees to be WD facilitators who would work directly with teachers. This model was decidedly in contrast to the prior two field trials in which research staff worked directly with classroom teachers.

In developing the model of coaching and support to teachers, we were informed by the emerging literature on professional development for educators and on adult learning. This work highlights the importance of providing opportunities for active learning through observation, meaningful discussion, practice, and reflection [30-32]. Research also suggests that professional development is best conceptualized as an ongoing process rather than a single event, and that professional development activities should be aligned with one's professional work [30,33-35] and incorporated into one's daily professional work [30,36-38].

Literature on adult learning and school reform emphasizes the importance of collective participation of teachers within schools, grouped by grade level, or of principals across schools [39-42]. A concept that became critical to our coaching model and our work with the Schools Committee and the Core Team is that supporting change at the organizational level requires linkages across levels in the system, not just within levels in the system [43,44]. Stated another way, while professional community matters at specific levels such as schools [45], it is critical to create communities of learners within and across the various levels of the organization [46,47]. As defined by Resnick and Glennan, nested learning communities are 'organizations in which all individuals and units are expected to upgrade their capacities continuously in accord with a shared set of instructional principles and strategies. In this design, instructional leadership, coupled with reciprocal accountability between 'layers' of the organization, provide professional learning opportunities specifically geared to the district's vision of instruction' [46].

The support provided to the teacher was primarily technical in that the WD facilitator was considered the expert in WD implementation practices and served as a mentor to the teacher. WD facilitators had expertise in the theory and practice of WD and classroom behavior management more broadly as well as the interpretation and use of data regarding teacher practices and student behavior. WD facilitators spent one day per week in the classroom with each teacher and supported teachers in bringing together the new knowledge of WD learned in the pre-implementation training with their craft knowledge of classroom teaching [48]. The WD facilitators spent most of their time working directly with teachers in classrooms, observing, planning, modeling and mentoring, and providing feedback [48,49].

Observations of teacher practices in the classroom provided the foundation of the WD facilitators' work. The facilitators used the WD implementation checklist each month throughout the entire school year to determine the type, amount, and focus of professional development. The checklist provided information regarding the occurrence and quality of teacher practices on both general practices and specific core elements of each component of WD. Using these data, the WD facilitators prioritized coaching needs and worked with the teacher to create a professional development plan that specified goals, target areas for mentoring, and coaching strategies and activities to be undertaken. WD facilitators supported teachers in WD practices through modeling of practices, guided practice, visits to other classrooms to observe WD implementation, conferences, and joint planning. The ability to work through trust with the teacher was a critical skill for facilitators; not all teachers welcomed a facilitator into their classroom or were open to the support the facilitator offered [50,51].

The extant literature provided little guidance about the pace and focus of coaching over the course of a year. We decided on a predetermined amount of coaching support, with WD facilitators spending additional time with teachers who needed more support. Each facilitator supported four schools, devoting one day per week supporting the WD teacher in each school. WD facilitators were trained during the first year of the trial by intervention team members who were part of the research staff.

### Systematic monitoring of intervention practices and support

In recent years, researchers have recognized that the delivery of intervention practices is usually variable and that this variability affects outcomes [1,16,52-59]. To understand the occurrence and quality of WD practices and the support delivered directly to teachers, we measured teachers' practices with regard to WD implementation as discussed above; facilitators' practices in supporting teachers; and the availability of resources such as materials, planning time, and release time for professional development, particularly those provided by the principal.

### Measures and data collection

Classroom observations of student behavior and teacher practices were conducted three times in first grade: baseline/autumn, mid-year/January, and spring/May. Each observation took four hours over two days, and did not disrupt the classroom activities. Teacher interviews about student behavior were conducted with first-grade teachers at the same three time points. When each cohort reached third grade, its current teacher was interviewed. In fall and spring of first grade and spring of third grade, students were assessed individually in a quiet area of the school on reading and reading-related skills; students were also asked about experiencing symptoms of depression and anxiety; see Additional File 1: 'Description of WD intervention, student sample, and measures of student outcomes'. School records were collected at the end of each school year.

### Measures of teachers' practices

We conducted classroom observations using a variation of teacher observation/student engagement [60]. In this time-sampling schema, a teacher's instructional practice and students' behavior are recorded minute by minute. For a teacher's instructional practice, observers code the instructional format and content of teaching. Eight instruction categories range from whole class to small groups to students working on their own, and include a category for non-reading instruction. Twenty content codes cover four domains: reading comprehension, word work, oral language and writing, and non-reading-related activities. The content codes were extended to include feedback in response to behavior (corrective, praise, punitive, directive). Inter-rater reliabilities of >0.80 are maintained. At the end of each timed observation, observers use the checklist of teacher's practices to rate the instructional and behavior management strategies exhibited during the session. The form parallels the WD implementation checklist and provides an independent measure of program implementation in WD classrooms, as well as information on classroom behavior management and instructional strategies in SC classrooms. Items were added to the teacher interview to assess the strategies that teachers used to engage with families and the level of caregiver response to the strategies.

### Measures of fidelity

The WD implementation checklist provided information about teacher practices along two dimensions, practices that were general to the classroom and practices that were intervention-specific. Thirty-six behavioral indicators precisely defining the core elements of the three intervention components were rated on whether defined practices occurred (yes/no) and with what quality (scale of one to six). A global rating was also given for each of the three intervention components. Measures of family-classroom partnership included attendance sheets for activities to which parents were invited, such as classroom orientation, class meetings, and the family read-alouds. The use of the home-link telephone line, a messaging system for teachers and parents, was monitored. Checklists were developed to rate the degree to which principals and facilitators fulfilled their clearly defined roles related to supporting the teacher and the implementation of the WD program.

### Statistical analyses and power

The analyses for Aim three, sustainability and scaling-up of WD practices, proceed logically from the analyses supporting the effectiveness trial of WD.

### Analyses for Aim one: Malleability of developmental paths

We are carrying out formal growth analyses to evaluate how WD affects the course of reading skills and achievement, aggressive behavior, and depressive symptoms. Intervention effects will be modeled as both mean differences in latent growth trajectories for the slope and differences in the covariance between intercept and slope by intervention group, a type of intervention by baseline interaction [61]. These analyses will include school- and classroom-level clustering. Following this series of multilevel analyses for single repeated measures, we will conduct multilevel growth analyses for first-grade through third-grade outcomes [62] to test for both main effects and interactions involving the intervention with baseline characteristics.

### Analyses for Aim two: Variation in impact

We will also examine whether the intervention affects children differently by using baseline measures of reading skills and aggressive behavior, as well as parent involvement. We have found that additive models [11,15], because they include nonparametric models with smooth changes in impact as a function of baseline, are excellent tools to distinguish the degree of benefit that different children receive from this particular intervention. A second method for examining variation in impact is examining how baseline interacts with intervention condition to affect growth trajectories [61,63-65]. These intervention-by-baseline models extend the univariate models into the growth curve framework, and allow changes in slope to be affected simultaneously by both intervention and baseline. Thus we will examine whether the best growth trajectory improvement from the intervention occurs more for higher- or lower-risk children.

A further set of analyses will be based on growth mixture modeling (GMM) [15,64,66] using Mplus software [62]. GMM allows fitting multiple growth trajectories, for example, early and late starters for aggression, and testing whether the intervention affects these groups differently. We can also carry out growth mixture analyses with a categorical distal outcome as well as time-to-event, or survival, measures (such as time of first suspension). In these general growth mixture models (GGMM) [15,64], parameters of individual growth trajectories, including intercepts, slopes, and higher-order shape parameters, may be influenced by baseline characteristics, intervention status, and time-dependent covariates. GGMM also allows individuals to follow a class of growth trajectories. An important part of this model is that class membership is an unobserved category variable. Nevertheless, like latent class analyses, GGMM permits both predictors and responses to be related to the unobserved class membership. Model selection for GGMM will be based on both the bootstrap likelihood ratio test and the Bayesian Information Criterion [67] with examination of model fit [64,68,69].

### Analyses for Aim three: Sustainability and scaling-up of WD practices

We will examine the extent to which the impact of WD on children's learning and behavior is explained by the level of by the teacher implementation, as well as school-level support, over time. We have successfully examined such implementation measures in the past [16] when we determined that poor implementation of the intervention fully explained the lack of improvement in some schools. Sustainability will be tested by comparing the practices and subsequent child outcomes for the WD teachers over two as well as three years with those of their SC counterparts for the first two years. Scaling-up will be tested by comparing the practices and child developmental outcomes for the original SC teachers in their last year with those in previous years and with those of WD teachers. The difference in SC measures across cohorts assesses this extendibility, and the power is expected to be similar to that for testing the intervention in cohort one because here each teacher serves as his or her own control.

### Statistical power

In cohort one, we expect to have power of 0.79 to test the WD main effect on end-of-first-grade reading when the true effect size is 0.25, compared against total variation in the sample. This calculation is based on specification of multivariate means, variances, and covariances from data from prior trials conducted in Baltimore. The prior studies provide estimates of each source of variation as well (children, classrooms within schools, and schools) [70]. It assumes that individual variation is twice as large as school variation, that classroom variation at the time of randomization was negligible, and that the variation in intervention impact by school is a third of the overall variation, with effect size. Because this earlier trial involved a smaller number of schools (nine instead of 12 schools) and a less comprehensive intervention compared with that in the present trial, we anticipate having higher statistical power than in the previous trial. In that trial, we were able to report significant main effects and interactions [10,16]. The power is nearly identical for third-grade main effect analyses as it is for end-of-first-grade analyses, even when we allow for 20% attrition, primarily from mobility. This loss in power through attrition is generally more than offset by the increase in power from growth curve analysis [61].

For testing whether the intervention improved teacher practices, statistical power is slightly higher, for the same size effect, compared with analyses of child outcomes. This difference occurs because the teacher measures are not subject to the added statistical error arising from child variation. Thus, we expect to have sufficient power to detect moderate size effects in this trial on teacher practices across cohorts. Our hypotheses state that the WD effects on the original WD teachers should increase from cohort one to cohorts two and three. We plan to test this with a two-level linear trend model across cohorts. A test for nonlinear trend (one DF) can also be carried out. The trend tests are expected to have higher power than our original tests of sustainability because there should be stronger improvements of these teachers over the cohorts.

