## Methods

### Overview of the design

The within-school design involved 12 public elementary schools and two first-grade classrooms within each school. Within each school, three consecutive cohorts of children were randomly assigned to first-grade classrooms as they enrolled. Classrooms/teachers were randomized to intervention condition in the first year, with one teacher assigned to WD and one teacher assigned to SC. Because every school had a WD and a SC classroom, schools served as blocking factors, and comparison of intervention effects could be obtained for each school. This two-level randomized block design allowed us to hold school, family, and community catchment area factors fixed while examining intervention effects at the classroom level, and examine main effects and test hypothesized variations in impact on the basis of variables such as gender, students' individual aggressive behavior, teacher self-efficacy, and classroom levels of aggressive behavior. Random assignment of children to classrooms allowed two classrooms within a school to be comparable at baseline and was extremely efficient in testing the main effect of a classroom intervention [5,6,16,17].

Aware of the possibility of intervention leakage with this classroom-based, within-school design, we implemented procedures that had successfully limited such leakage in the prior trials, such as meeting with principals monthly [16]. In addition, the SC teachers received training and support in WD as part of the design in the third year of the trial. We found no evidence of contamination in the schools with internal controls in either of the first two trials [5,16] or in this trial.

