### Classrooms/teachers

In April 2003, all 37 first-grade classrooms/teachers in the 12 schools participating in the randomized field trial were randomly assigned to condition. In each school, one teacher was randomly assigned to be a WD classroom/teacher, one was randomly assigned to be a wait-listed SC classroom/teacher, and all other first-grade teachers were randomly assigned to be nonparticipating classrooms/teachers. Teachers in both WD and SC classrooms were followed as they taught three consecutive cohorts of first graders. In a type of wait-listed control, SC teachers who served as controls for cohorts one and two were trained in the third year to deliver WD to cohort three first-grade students. The effectiveness trial relied on efficient within-school comparisons of WD and SC for cohort one and cohort two students from first to third grade. The sustainability question centered on whether WD teachers' practices remained high or fell off across the three cohorts. The scale-up question centered on whether the practices of the former SC teachers improved--as well as the consequent child outcomes--when they were trained to deliver WD.

While each of the 12 schools maintained the design by having one WD classroom and one SC classroom each year for three years, there were changes at the teacher level as teachers left the school. We anticipated that some teachers would change over the years, and we established a protocol for such changes. We stipulated that if a teacher left, the classroom would not change condition and the new teacher would be assigned the departing teacher's intervention status. If the replacement was a teacher already in the school, our protocol stipulated that this teacher could not have previously been assigned to a condition (WD or SC) within the trial. The patterns of teacher mobility are shown in Figure 1. There were no changes in either WD or SC teachers in schools one to five; the same teachers taught the WD and SC classrooms for all three years of the trial. Schools six to 12 experienced some degree of teacher mobility.

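### With 12 pairs of teachers, power for teacher practices is not higher than for child outcomes at the same standardised effect, and adequate power for moderate effects is not supported

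*Protocol article*

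**What the plan says.** The Protocol article, Statistical power, gives one numerical power figure: "In cohort one, we expect to have power of 0.79 to test the WD main effect on end-of-first-grade reading". The effect behind that figure is 0.25, scaled to the total SD among the children. On the variance components it says "It assumes that individual variation is twice as large as school variation", and it takes classroom variation at randomisation to be negligible.

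The next paragraph turns to teachers: "For testing whether the intervention improved teacher practices, statistical power is slightly higher, for the same size effect, compared with analyses of child outcomes". The explanation is that teacher measures escape the error that child variation adds. From this it concludes that "we expect to have sufficient power to detect moderate size effects in this trial on teacher practices across cohorts". It gives no separate power figure, effect-size scale or variance for teacher practices.

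The number of teachers is fixed elsewhere. Overview of the design: "The within-school design involved 12 public elementary schools and two first-grade classrooms within each school". Classrooms/teachers: "In each school, one teacher was randomly assigned to be a WD classroom/teacher, one was randomly assigned to be a wait-listed SC classroom/teacher". SC teachers are untreated controls in cohorts one and two only, because they are trained in WD in the third year. Measures and data collection has teacher practices observed three times in each first-grade year: autumn baseline, mid-year and spring.

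**The concern.** The comparison holds the effect size constant but changes what it is measured against. For reading, 0.25 is a fraction of the total SD among children. The test compares class means: blocking on school removes the school component, and averaging over a class shrinks the child component. For practices there is one teacher per arm per school. An effect expressed in teacher SDs is set against that same SD, and there are no children to average over. Removing child error also removes the averaging that makes the class mean precise relative to the child SD, so the stated reason does not lead to the stated result.

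Teacher practice is central to Aim three, which is the subject of this article. A reader who takes 0.79 as a floor for practice effects of 0.25 would overrate what 12 pairs can show, and would give a non-significant WD-SC difference in practices more weight than it can bear.

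**Working it through.** **Inputs from the article.** 12 schools; one WD and one SC teacher in each, so 12 pairs and 11 df; child effect 0.25 of total SD; child variance 2/3 individual and 1/3 school; classroom variance about 0; two cohorts with an untreated SC control; three practice observations a year.

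**Assumptions, not in the article.** Two-sided alpha 0.05; within-school correlation of the two teachers' scores, rho, from 0 to 0.5 (1/3 if the school share of child variance is borrowed); moderate effect = 0.5 teacher SD; children per class m; correlation 0.5 between any two occasions for the same teacher; the same teacher in both cohorts.

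**Method.** Paired contrast. Power comes from the noncentral t with 11 df and noncentrality dz × √12, where dz is the mean difference divided by the SD of the within-school difference.

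**1. The article's 0.79 for reading.** Variance of the within-school difference = 2 × (2/3)/m + τ², where τ² is the variance of impact across schools. The wording on τ² is incomplete, so the figure cannot be reproduced uniquely.
- m = 18, τ = 0.25/3: 0.0741 + 0.0069 = 0.0810; SD 0.285; dz = 0.25/0.285 = 0.88; power 0.791.
- m = 22, τ² = 0.25²/3: 0.0606 + 0.0208 = 0.0814; dz = 0.88; power 0.789.
- τ² literally one third of total variance, m = 10 to 25: power 0.21 to 0.25.

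So 0.79 is reachable under two reasonable readings, both with dz about 0.88.

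**2. Teachers, one cohort, one unadjusted score.** dz = d/√(2(1 − rho)).

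| d (teacher SD) | rho = 0 | rho = 1/3 | rho = 0.5 |
|---|---|---|---|
| 0.25: dz | 0.18 | 0.22 | 0.25 |
| 0.25: power | 0.087 | 0.105 | 0.124 |
| 0.5: power | 0.201 | 0.278 | 0.353 |

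At 0.25, dz is 0.18 to 0.25 for teachers against about 0.88 for children. Power of 0.79 needs dz = 0.877. In one cohort that means rho of about 0.96 at d = 0.25, or about 0.84 at d = 0.5.

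**3. Teachers, average of cohorts one and two.** The variance of a teacher's two-year mean is (1 + 0.5)/2 = 0.75, so dz is divided by √0.75 = 0.866. At d = 0.5, power is 0.253, 0.353 and 0.446 for rho 0, 1/3 and 0.5.

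**4. Teachers, four post-baseline observations over two cohorts, adjusted for baseline.** The variance of the mean of four is (1 + 3 × 0.5)/4 = 0.625. Baseline adjustment removes 0.5² = 0.25 and leaves 0.375, so dz is divided by √0.375 = 0.612.
- d = 0.5: 0.446, 0.608 and 0.731 (0.44, 0.60 and 0.72 with 10 df).
- d = 0.25: 0.15, 0.20 and 0.25.

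**5. Detectable WD-SC effect at 80% power** (dz = 0.889).

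| Analysis | rho = 0 | rho = 0.5 |
|---|---|---|
| One cohort, unadjusted | 1.26 | 0.89 |
| Two-cohort average | 1.09 | 0.77 |
| Repeated, baseline-adjusted | 0.77 | 0.54 |

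**6. Higher within-school correlation.** At d = 0.5 and rho = 0.8, the two-cohort average has power 0.82. The repeated, adjusted analysis reaches 80% at rho of about 0.6, from 1 − (0.5/(0.612 × 0.889))²/2 = 0.58. At d = 0.25 and rho = 0.9, power is 0.42 in one cohort and 0.82 in the repeated, adjusted analysis.

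**The case against.** **Meaning of the same size effect.** The article names no yardstick for teachers. If one raw effect on a common child scale was meant, with classroom variation negligible, dropping child error would raise power and the sentence could be defended. But the article does not say this, and practice scores come from their own observation codes and checklists. At a minimum the scale has to be stated.

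**One cohort or several.** The conclusion about moderate effects refers to analyses across cohorts, and practices are observed repeatedly with a baseline. The one-cohort 0.20 to 0.35 is therefore not the figure that answers it; steps 3 and 4 are. This objection stands. The fuller analyses bring power nearer to adequate but still below 0.80 at d = 0.5 for rho up to 0.5.

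**Assumed inputs.** Alpha, rho, the time correlations and the value of moderate are all assumptions, and a high enough rho would rescue the claim. This stands too, so the conclusion about moderate effects can be called unsupported but not shown to be false.

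**A stronger reading.** A reader might infer that null results will be taken as proof of no fall-off or of successful transfer to SC teachers. The article does not support that. It contains no rule that treats non-significance as equivalence. Those questions also rest partly on other tests, namely the trend across cohorts in WD teachers and the change in SC teachers against their own earlier years. The calculations here say nothing about the power of those tests.

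**Conclusion.** The point holds for the between-arm WD-SC contrast when effects are measured in teacher SDs. The sentence ranking teacher power above child power, and the reason given for it, are wrong on that scale. At 0.25, power is about 0.09 to 0.12 in one cohort and no more than about 0.25 in the most favourable two-cohort analysis examined, for rho up to 0.5, against a stated 0.79 or better.

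The conclusion on moderate effects across cohorts is not supported under the stated assumptions: at 0.5, about 0.25 to 0.45 for the two-cohort average and about 0.45 to 0.73 with repeated measures and baseline adjustment. A within-school correlation of about 0.8 would supply adequate power for the two-cohort average, and a lower one (about 0.6) for the adjusted analysis, but the article gives no evidence on this correlation. Large practice effects, near 1 SD, are within reach of the design. Severity: should-fix.

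**What to change.** In Statistical power:
- Delete the sentence that ranks teacher-practice power above child-outcome power, with its rationale.
- Replace the conclusion about moderate effects with the scale of the effect (SD between teachers) and the WD-SC effect detectable at 80% power from 12 pairs, with alpha, within-school correlation and time correlations stated. On the assumptions used here: about 0.9 to 1.3 teacher SD in one cohort unadjusted, 0.8 to 1.1 for the two-cohort average, and 0.5 to 0.8 with repeated measures and baseline adjustment. Practice data from the earlier Baltimore trials, if they exist, would be a better source for the correlations.
- Say that these figures cover the between-arm contrast only, not the WD cohort trend or the SC own-control comparison.
- Report practice contrasts as estimates with 95% confidence intervals.

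The cost is wording and a less favourable stated power. Design, sample and tests do not change.
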